# Reading intervention for students with intellectual disabilities without functional speech who require augmentative and alternative communication: a multiple single-case design with four randomized baselines

**DOI:** 10.1186/s13063-023-07452-4

**Published:** 2023-06-27

**Keywords:** Intellectual disabilities, Augmentative and alternative communication (AAC), Reading intervention, Phonological awareness, Letter-sound correspondence, Shared reading, Sight words, Decoding, Multiple single-case design

## Abstract

**Background:**

Literacy is one of the most important skills a students can achieve, as it provides access to information and communication. Unfortunately, literacy skills are not easily acquired, especially for students with intellectual disabilities who require augmentative and alternative communication (AAC). There are many barriers to literacy acquisition, some due to low expectations from parents and teachers and lack of evidence-based reading programs and reading materials adapted for AAC. Barriers as a result of extensive support needs is also a real factor. This trial aims to deliver reading instructions to 40 students with intellectual disabilities who require AAC and contribute in the debate on how to best support this population through reading instructions to maximizes their reading skills.

**Methodology:**

Forty non-verbal or minimally verbal students (age 6–14) with intellectual disabilities who require AAC will be part of a reading intervention with a multiple single-case design with four randomized baselines. The intervention period will last for 18 months and will commence in March 2023. The students will receive the intervention in a one-to-one format, working systematically with a reading material that contains phonological awareness and decoding tasks based on the Accessible Literacy Learning (ALL) developed by Janice Light and David McNaughton. All the teachers will be trained to deliver the reading intervention.

**Discussion:**

The reading material “Lesing for alle” (Reading for all) is based on and follow the strategies behind the research of ALL. The current trial will through a reading intervention contribute to move beyond only teaching sight words and combine several reading components such as sound blending, letter-sound correspondence, phoneme segmentation, shared reading, recognition of sight words, and decoding. The strategies and methods in use is built on the existing science of reading, especially what has been effective in teaching reading for students with intellectual disabilities who require AAC. There is limited generalizability of prior findings in reading-related phonological processing interventions to different populations of them who use AAC specially outside of the USA. More research is needed to understand how programs designed to improve reading skills across other settings understand the program’s long-term effects and to study the effectiveness when delivered by educators who are not speech language therapists or researchers.

**Trial registration:**

NCT05709405. Registered 23 January 2023.

**Supplementary Information:**

The online version contains supplementary material available at 10.1186/s13063-023-07452-4.

## Background

The importance of possessing literacy skills in today’s society should not be underestimated. Those who are literate benefit from increased access to education, employment [1], social interaction [2], mainstream technologies, and a wide range of information resources [3]. Literacy skills also have a powerful impact on communication and language development, on the improvement of cognitive development, and in the advancement of learning for individuals with intellectual disabilities (ID) and autism spectrum disorder (ASD) who require augmentative and alternative communication (AAC) support [4]. Literacy skills can enhance benefits even more for individuals with complex communication needs. Once an individual can read, the ability to communicate provides increasing possibilities for better communication with partners as well as larger access to a wider variety of opportunities [5, 6]. With improved communication, individuals will, to a lesser extent, need to rely on others to provide pictures or graphic symbols to express their ideas [4, 7]. Andzik and Chung [8] point out that individuals with complex communication needs may have intermitted or limited access to AAC during their school years, and their educational teams may not be equipped to provide AAC. Limited AAC may lead to a range of barriers throughout the life span [9].

Students with complex communication needs that require AAC are often excluded from phonological approaches to literacy. Browder et al. [10] found only 10% out of 128 studies focused on teaching reading skills that targeted phonics or phonemic awareness to students with intellectual disabilities considered to be moderate to severe in disability severity. Most literacy approaches require verbal production of speech sounds, which are particularly difficult for individuals with complex communication needs. Despite challenges with the spoken production of sounds, research has reported positive outcomes in participation in phonological interventions when they are adapted to meet the needs of students who require AAC [11-16].

A reading program that has been used in several studies is Accessible Literacy Learning (ALL). ALL is an evidence-based approach designed to teach reading skills to students with various intellectual disabilities, ASD, cerebral palsy (CP), and Down syndrome (DS) [3]. ALL combines a synthetic and analytical approach in reading instruction and is designed according to recommendations from the National Reading Panel [14].

## Previous relevant work

The body of research on reading instructions and intervention for students who require AAC is small [17], because it is conducted with a low prevalence population [11]. This contributes to little empirical evidence, and it can be difficult to measure the effectiveness of these programs, which are specifically designed to teach reading skills to students with intellectual disabilities, without functional speech [16].

It is also a challenge to build a cumulative knowledge base because of the wide variety of information and assessments reported in reviewed studies. The evidence-based research for reading interventions for students who require AAC consists of a small group of single-subject-design studies that use different measures and teaching strategies and demonstrate varying degrees of success [11]. Most studies have also focused on identifying sight words [10], but sight word instruction alone is not likely to result in a child with disabilities to learn reading [18].

A study by Fallon et al. [19] met the minimum standards of evidence established by the What Works Clearinghouse (WWC) [20] and provided strong evidence of intervention effects and moderate evidence of generalization. The result of this study, along with those of Millar et al. [21], were used to develop a literacy curriculum designed for children who use AAC [4]. The Accessible Literacy Learning curriculum [3] incorporated the instructional strategies and materials shown to be effective from these studies and is a good example of research informing practice [11].

A review of Yorke et al. [16] examined interventions from 1980 to 2019 that focused on improving basic literacy skills, such as phonological awareness (sound blending and segmentation), letter-sound correspondences, and decoding of simple words. They looked at the effect of studies with designs that were adapted to the needs of individuals with limited or absent speech and who used AAC. Seven of 22 interventions addressed ALL [4, 19, 22-25] and Westover, referred in Yorke et al. [16]. These studies showed an increase of 39% in total and large effects (Tau-U = 0.78) [16].

Another review, Bakken et al. [26], investigated the effects of reading and writing interventions for students aged 4–19 with intellectual disorder using randomized controlled trials (RCTs) and quasi-experimental designs (QEDs). The overall mean effect size from the reading interventions for trained reading was large (*g* = 0.95, 95% CI = 0.51, 1.28). However, the participants in these studies had varying levels of verbal skills, and only one study, Ahlgrim-Delzell et al. [27], specified that all the students were nonverbal and used AAC.

Barker et al. [11] identified eight articles in their review that reported teaching phonological awareness, individual word reading, and evidence-based literacy instruction for children with severe speech impairment who used AAC. Each study used a single-subject research design and was evaluated regarding whether it met Kratochwill et al. [20] minimum evidence standards (strong, moderate, or no evidence of an effect). Only five studies met criteria for strong evidence considering the effect of instruction on outcomes.

It was recommended that teachers chose an evidence-based reading program based on explicit teaching, corrective feedback, scaffolding, rewards, repetitions, and systematic teaching of phonological awareness and phonetic skills to ensure that students had opportunities to generalize their skills [7, 18, 28, 29]. Yorke et al. [16] also emphasized adapting an intervention so that verbal responses were not required, provided explicit practice with the skills, focusing on one to four foundational reading skills (directly corresponding to those measured), and included direct instruction procedures (i.e., introduction, model, guided practice, and independent practice with frequent positive or corrective feedback, in the intervention).

Reichow et al. [30] pointed out that additional experimental studies, in which there is efficacy of beginning reading interventions for children with intellectual disabilities, were needed. These additional studies could require several years of intensive intervention to demonstrate progress and allow for better understanding of possible outcomes.

It is important to describe participants characteristics prior to instructions, descriptions of the experimenter’s designed or modified standardized assessments, and the use of a strong research design. There is also a strong need for standardized assessments of both phonological awareness and reading that do not require speech responses [11].

Yorke et al. [16] point out that interventions should shift away from being administered by researchers towards administration by other communicative partners (e.g., teachers).

Future studies must consistently quantify participants’ cognitive, linguistic, and literacy levels and clearly describe the format and frequency of the intervention. It will be important to determine best practices related to intervention guidelines [16]. Future reading intervention studies for students with intellectual disabilities should include at least a 1-year follow-up in light of existing evidence of a fade-out effect within the first year or two following interventions [26].

## Methodology

### Aims

This trial investigates whether non-verbal or minimally verbal students with intellectual disabilities, who require AAC, can acquire foundational reading skills through instructions in phonological awareness (sound blending and phoneme segmentation), letter-sound correspondence, shared reading, sight words, and decoding by working systematically and explicitly with the reading program “Lesing for alle” (“Reading for All”). The adapted reading material has been prepared and designed in line on the basis of the research of the evidence-based reading program Accessible Literacy Learning (ALL) [3].

The research questions are as follow:Is there a functional relationship between the use of “Lesing for alle” and increased accuracy of sound blending by students age 6–14 with intellectual disabilities who require AAC?Is there a functional relationship between the use of “Lesing for alle” and improved acquisition of letter-sound correspondence by students age 6–14 with intellectual disabilities who require AAC?Is there a functional relationship between the use of “Lesing for alle” and improved acquisition of phoneme segmentation by students age 6–14 with intellectual disabilities who require AAC?Is there a functional relationship between the use of “Lesing for alle” and improved acquisition of recognition of sight words by students age 6–14 with intellectual disabilities who require AAC?Is there a functional relationship between the use of “Lesing for alle” and improved acquisition of decoding by students age 6–14 with intellectual disabilities who require AAC?Is there a positive and strong correlation between increasing skills from 1–3 to 4–5? Meaning, is there a transfer from lower-level skills (phonological skills) to decoding skills?

As this trial is a multiple single-case design, there were no comparator interventions chosen.

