#### Design of the material

The tasks in sound blending, letter-sound correspondence, phoneme segmentation, sight words, and decoding are divided into four rectangular squares with a black frame in an A4 format. There is a symbol, letter, or word in each square. There is a corresponding instruction on each back of the assignment. The instructions lay down guidelines for what the teacher should say and how. The correct answer, target sound, or target word is marked in green so that the teachers can see what is correct. The instructions are short to adapt to the amount of verbal instruction the students can handle. Words and letters are written in small letters, with the font Arial, and the font size varies according to the different tasks. The tasks in “Shared reading” are made with images taken from the ALL App [45]. Through levels 1, 2, and 3, students encounter many words and symbols, about 350. The words are taken from McArthur-Bates Communicative development Inventory [46]. The entire material is made in the program InPrint and consists of Wigdit symbols [47]. Wigdit symbols are an English symbol layout that was created to support the reading and writing development of children who had difficulty cracking the reading code [48].

The material contains the following:*Level 0*. One folder (with about 60 tasks in explicit instruction in sound blending, letter-sound correspondence, shared reading, phoneme segmentation, sight words, and single-word decoding). Explicit instruction involves the teacher specifically identifying the skills for students to be taught in the lesson and then directly modeling the skill [49]. The current intervention will make use of explicit instruction through progressive scaffolding, which allows for systematically modeling of the concept, guided practice, and eventually to independence.

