During the first step, the teacher is modeling for the student what will be required of them in each task and the student is a passive observer. The only expectation of them is that they are paying attention to the teacher. The teachers must follow the various scripts in the various reading components. The first step in the task is for the teacher to name all the four symbols and say “I’m going to say a word, listen to the word.” The teacher says the target word (for example seal). “Ssseeeaaalll,” the teacher says the word gradually faster, “sseeaall,” and finally say it normally, “seal.” Then, the teacher says “now I look at the symbols” and choose the symbol for “ssseeeaaalll.” The teacher points to the symbol for seal and at the same time says “ssseeeaaall” is a seal.”

During the second step, guided practice, the student is expected to be active in the lesson and is encouraged to point to the target item as well. In this step, the students get support to complete the tasks correctly together with the teacher. The teacher starts by saying “let’s do the task together.” It is the same script as in the modeling phase, but the teacher encourages the student to do it together.

During the final step, independent practice, students must perform independently. Teacher emphasizes and says “now it’s your turn, tap the glue icon.” If the student points to the correct symbol, the teacher says “good, g-llluuueee is glue.” The teacher points and confirms that the student has chosen the correct symbol. If the student answers incorrectly, the teacher corrects immediately and says “You pointed to xx (wrong answer), we have to find glue.”*Level 1*. Eight folders (with about 120 tasks in sound blending, letter-sound correspondence, and shared reading in each folder)*Level 2*. Thirteen folders (with about 120 tasks in sound blending, letter-sound correspondence, phoneme segmentation, single-word decoding, and shared reading in each folder)*Level 3*. Ten folders (with about 150 tasks in sound blending, letter-sound correspondence, phoneme segmentation, sight words, single-word decoding, advanced word decoding (for example, words with multiple consonant accumulations), not phonetic word pictures, recognition of high-frequency words, and shared reading in each folder)

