#### How the data should be described

Each student will receive a specific number (subject ID) throughout the intervention. The list of names and numbers will be stored in a locked filing cabinet in a locked office where only the researcher has the key. The numbered data will be stored in another locked filing cabinet, i.e., separate from the list with names and numbers. All tests carried out, the registration forms, and the CDIs will be marked with the students subject ID from the randomization list.

The data that will appear on each test will list the number of correct and incorrect responses. The data that will appear on student forms from each work session will list also the correct and incorrect responses as well as the time used. It is particularly important to measure the students work progress, because they have to achieve at least 80% correct responses before they can move on to the next folder.

The data that will be collected on social validity will inform the researchers whether the students have liked working on the reading program and if they would like to continue. For children who use AAC to communicate, assessing consumer satisfaction should involve the AAC user to the greatest extent possible [52]. Directly asking the student about their experiences during and after the intervention may increase intervention relevance to the student and possibly increasing motivation to adhere to and complete the intervention [53]. In connection with data from the teachers’ survey, they will say something about the teachers’ experiences with the reading program and the reading material.

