#### Statistical analysis plans

Generalized estimating equation (GEE) with work matrix of first-order autoregressive factor will be used to the effects of the implementation of the intervention after the baseline assessment. Missing data will be treated as missing at a random mechanism via restricted maximum likelihood. The adopted significance level is 0.0125 (due to the four correlated outcomes, reducing the false discovery rates). For interobserver quality check, we will calculate the interobserver agreement using intraclass correlation (ICC) [55]. There are no plans to conduct additional analyses (e.g., subgroups or adjusted analyses).

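### Research question 6 reads correlated gains as transfer, although the 80% folder rule can make those gains correlate with no transfer at all

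*Protocol article*

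**What the plan says.** In the Aims section, research questions 1-3 cover sound blending, letter-sound correspondence and phoneme segmentation. Questions 4-5 cover sight words and decoding. Question 6 then asks "Is there a positive and strong correlation between increasing skills from 1–3 to 4–5? Meaning, is there a transfer from lower-level skills". The interpretation that it gives at once reads in full: "Meaning, is there a transfer from lower-level skills (phonological skills) to decoding skills".

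The section Design of the material sets out the order of teaching:

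- Level 0 is one folder with "about 60 tasks in explicit instruction in sound blending, letter-sound correspondence, shared reading, phoneme segmentation, sight words, and single-word decoding".
- Level 1 has "Eight folders (with about 120 tasks in sound blending, letter-sound correspondence, and shared reading in each folder". It contains no segmentation, decoding or sight words.
- Level 2 has "Thirteen folders (with about 120 tasks in sound blending, letter-sound correspondence, phoneme segmentation, single-word decoding, and shared reading in each folder". Segmentation and decoding come back here.
- Level 3 has ten folders of about 150 tasks, and sight words come back here.

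The section How the data should be described adds the progression rule: "they have to achieve at least 80% correct responses before they can move on to the next folder". The Statistical analysis plans section describes a GEE for the intervention effect and states "There are no plans to conduct additional analyses (e.g., subgroups or adjusted analyses".

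**The concern.** A correlation between two gains supports a transfer reading only if nothing else in the trial ties them together. Here the teaching schedule does. A student who is slow on the phonological folders spends most of the calendar in Level 1 and is taught almost no decoding. A student who is quick is taught a great deal of it. Gains in skills 1-3 and skills 4-5 then rise together through the amount of decoding teaching received, whether or not phonological skill helps decoding.

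There is a second route. Phoneme segmentation, one of the supposedly upstream skills, is itself absent from Level 1 and returns in the same Level 2 folders as decoding, so shared exposure links those two gains directly.

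At stake is the conclusion on one of six research questions: the trial could announce transfer where none exists.

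**Working it through.** The article gives no correlation, threshold or power for question 6, so there is no figure to reproduce. The check has three parts.

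**1. How much material lies behind the rule** (task counts from Design of the material, all approximate)

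- Level 0: 60. Level 1: 8 × 120 = 960. Level 2: 13 × 120 = 1,560. Level 3: 10 × 150 = 1,500.
- Total: 60 + 960 + 1,560 + 1,500 = 4,080.
- Before the first Level 2 decoding folder: 60 + 960 = 1,020, or 25% of the material.
- Before the first Level 3 sight-word folder: 1,020 + 1,560 = 2,580, or 63%.
- Level 0 share: 60 / 4,080 = 1.5%.

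**2. Correlation of gains when transfer is zero**

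From the article: 40 students, 18 months, four-option tests. Assumed, because the article does not give them: median 6, 10 or 14 months to pass Level 1; coefficient of variation (CV) of the learning rates 0.3 or 0.6; measurement noise 0.5 or 1.0 SD of the gain; saturating growth from chance level. Phonological and decoding learning rates are drawn independently, so there is neither transfer nor shared ability. With T the time to pass Level 1, inversely proportional to the phonological rate, decoding grows only during max(0, 18 − T) months. There were 1,500 runs for each of 24 settings. Selected settings:

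| Median T (months) | CV phonological | CV decoding | Noise | Mean r | P(r ≥ 0.5) |
|---|---|---|---|---|---|
| 6 | 0.3 | 0.6 | 1.0 | 0.15 | 1% |
| 6 | 0.6 | 0.6 | 0.5 | 0.44 | 36% |
| 10 | 0.3 | 0.6 | 1.0 | 0.31 | 9% |
| 10 | 0.6 | 0.6 | 0.5 | 0.62 | 91% |
| 14 | 0.6 | 0.3 | 0.5 | 0.74 | 100% |

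- Over all 24 settings, mean r is 0.15 to 0.74 and always positive.
- r exceeds 0.312, the two-sided 5% critical value at n = 40, in 16% to 100% of runs. At the article's 0.0125 level the critical value is 0.391.
- With the same start of decoding for everyone and all else unchanged, mean r is 0.01 and r ≥ 0.5 occurs in 0% of runs. In this model the gate alone produces the correlation.
- Crediting Level 0 with 1 or 3 months' worth of ungated decoding teaching (median 10 months, both CVs 0.6, noise 0.5) lowers mean r from 0.62 to 0.59 or 0.53.
- Two other zero-transfer models with different assumed pace and noise gave mean observed r of 0.22-0.43 and of 0.26-0.57. In the second, r ≥ 0.5 occurred in 4-79% of trials.

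Sampling error at n = 40, for an observed r of 0.5: Fisher z = atanh(0.5) = 0.549, standard error 1/√37 = 0.164, so z ± 1.96 × 0.164 = 0.227 to 0.871. This back-transforms to 0.22 to 0.70.

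**3. Whether adjustment or time order rescues the transfer reading**

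- With phonological knowledge driven by folder pace, it correlates 0.88-0.98 with months at Level 2 or above. Adjusting for those months leaves almost nothing to analyse.
- With zero transfer, the adjusted correlation averaged 0.00-0.01, significantly positive in 2-3% of trials. With true transfer built in, it still averaged only 0.01-0.05, significant in 3-5%.
- When some phonological variation was made independent of pace, power to detect true transfer was 10-29%.
- An unadjusted time-ordered correlation (skills 1-3 gain to month 12 against decoding gain from month 12 to 18) still averaged 0.08-0.40 with zero transfer, because students ahead at month 12 are those already in Level 2.

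**The case against.** The strongest reply is that the article only poses a question. It sets no coefficient, cut-off or test for question 6, and as a condensed account it may leave that analysis to the full protocol. This stands: no missing analysis is alleged. The sentence that equates correlation with transfer is nevertheless in the text, and the teaching order described in the same article undercuts it.

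Second, Level 0 already contains decoding and sight words, and the Secondary outcomes section says half of the 20 decoding words are novel. Both are true. Level 0 is too small to change the result much, and novel words do not help when instruction in decoding as a skill is itself delayed by the folder rule.

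Third, the size is assumed. That also stands. Only the expected sign follows from the article. In some settings the mean correlation is one that few would call strong.

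Two stronger readings are tempting. A reader might infer that adjusting for decoding exposure would separate transfer from teaching. A near-zero adjusted correlation under zero transfer looks like proof, but the adjusted correlation stays almost as close to zero when transfer is real. A reader might also infer that the Statistical analysis plans section forbids such an adjustment. Its sentence concerns additional analyses, and question 6 is a listed research question, so the wording is unclear rather than prohibitive.

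**Conclusion.** The point holds as a limit on interpretation. With decoding and sight words placed behind 80% mastery of earlier folders, a positive correlation of gains is expected without transfer, so question 6 as glossed can yield a false claim of transfer. Confidence is high for the sign and mechanism, which follow from the level contents and the progression rule. It is low for the size: the simulated mean r of about 0.15 to 0.74 rests on assumed pace, spread of learning rates and noise, so a strong value is possible but not assured.

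It does not follow that transfer is absent, or that any observed correlation would be wholly an artefact. The design cannot tell these cases apart. The point concerns one research question and leaves questions 1-5 untouched.

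**What to change.** 1. In Aims, delete the sentence "Meaning, is there a transfer from lower-level skills (phonological skills) to decoding skills". Report the correlation of gains with a confidence interval as an association, and state that the 80% folder rule alone can produce a positive value.
2. As a sensitivity analysis, add the correlation adjusted for time taught at Levels 2-3 and for start group, provided the session records identify the level. The article says that session time, and whether explicit instruction or reading tasks were used, are registered. It does not name folder or level as a recorded item, so this should be confirmed.
3. State in Statistical analysis plans that question 6 is not covered by the sentence on additional and adjusted analyses.
4. Say plainly that the adjusted estimate has little power and cannot rule transfer in or out, because phonological gain and time at Level 2 or above are nearly collinear. If a time-ordered correlation is shown, say that without adjustment it too is affected by the folder rule.

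The cost is wording and one further analysis. No new data collection is needed if the records identify the level. The price is a weaker claim than transfer.
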